### Ethics

The study is conducted according to The Declaration of Helsinki and Good Clinical Practice guidelines and is approved by the local ethics committee (Case number: 1–10-72-1008-17) and Danish Health Authorities (EudraCT number: 2017–000992-10, case number 2017043424). The study is monitored by the Good clinical practice (GCP) unit at Aalborg and Aarhus University Hospitals.

All patients with a biopsy with AIN will be approached by a physician and will be given oral information as well as a detailed written information. Provided the patients feel they have had sufficient time to consider their potential involvement, consent may be sought immediately. Otherwise, time is allowed for potential participants to consider the information provided, discuss the trial with their family and friends, and decide whether to take part before consenting. Informed written consent is obtained from all patients who agree to enter the study.

### Data protection

All data activities in the study are documented and stored in the web-based REDCap data capture application (https://redcap.au.dk) and is administered by Aarhus University. This system is situated in a Server Park in Central Denmark Region using firewall and Threat Management Gateway. Backup of data is performed on weekly basis and data transactions fulfil the requirements requested by the Danish Data Protection Agency.

### Time schedule

The estimated trial duration is 8 years. The study was launched at the first centers on Sept 1, 2017. Since then, all 11 Danish nephrology centers have been enrolled caring for a population of approximately 4.7 million adults. Currently, 30 patients have been included, and 82 patients have been screened. Unpublished data suggest that approximately 15 patients per year is diagnosed with AIN in the Middle- and Southern regions of Denmark covering approximately 2.0 million adults. With the participation from all Danish nephrology centers, we expect recruitment to be feasible within the suggested time-frame.

## Discussion

The study will provide important information on the effects of prednisolone treatment in AIN and as well as prognostic information relevant for future use of biomarkers and histology. Ultimately, this would lead to improved and evidence based clinical guidelines for the treatment of AIN. For years, treatment of AIN has been empirical, steered by clinical judgement and influenced by the results of retrospective studies hampered by selection bias. Many patients receive steroid treatment despite the lack of convincing evidence from randomized clinical trials. Treatment is driven by the potential long term benefits associated with the conservation of renal function, as chronic kidney disease has serious detrimental effects on morbidity and life expectancy. However, considering the potential serious adverse effects associated with steroids, the benefits of treatment should be better documented.

The prospective design with randomization to treatment should minimize selection bias for the patients who accept to participate. However, a selection prior or during recruitment is still a risk in this randomized design. Preferences by treating physicians may still determine and affect eligibility for participation in the trial. Thus, a systematic screening log of patient with renal biopsy proven AIN has been included allowing further characterization of the patients not included in the trial. This should enable us to identify if particular patient groups are withheld participation in the study. The study is a national Danish study and the Danish population is mainly of a Caucasian race and will therefor probably mainly include a Caucasian population. This will result in a uniform cohort but limit the generalizability to other populations with different racial composition.

Although we have no data to support this, it is likely that the threshold for renal biopsy in suspected AIN differs between centers depending on local practices, tradition and logistics. A direct consequence of this study may be that biopsy frequency increases to facilitate study participation. The requirement for a renal biopsy ensures the diagnosis of AIN and randomization minimize the risk of confounding due to different biopsy practices.

The open-label design may introduce bias both with respect to in the adjunctive therapy as well as in the reporting of outcomes both from participants and from the treating physicians. Additional treatment, including renal replacement therapy is decided by the treating physicians; however, is expected to follow international guidelines [45, 46, 50], Blinding was considered, but was discarded since a genuine blinding of high dose prednisolone treatment is difficult based on the significant adverse effects, including prominent leukocytosis. An inevitable and direct consequence of the open-label design is a risk of cross-over between treatment groups e.g. due to preferences of patients or treating physicians. To accommodate this, both “intention-to-treat” and “treated-as” analyses are planned. Nevertheless, a high cross over rate could influence and dilute a possible significant result, which is difficult to overcome statistically.

Although steroid treatment is often used in AIN there is limited evidence from clinical or retrospective trials to support this. Thus, considering the known and potential serious adverse effect of steroids, we believe that it is medically and ethically justified to include a trial arm that do not receive active treatment. Notably, recent studies, such as the PEXIVAS trial, addressing autoimmune disease in which the efficacy of steroid treatment seems evident, have shown that a reduction in steroid dose is safe and reduces adverse events [51].

The power calculations are based on a clinical relevant difference in eGFR of 10 ml/min/1.73m^2^ as well as additional assumptions based on previous observations from retrospective trials [29–31]. As in other trials there is a risk that the assumptions are wrong and the study is underpowered, in particular if there is significant drop out or cross-over. It may be argued that a difference in eGFR less than 10 ml/min/1.73m^2^ at 3 months could be clinical relevant, in particular in late stage CKD. Thus, a negative outcome of the trial cannot exclude a minor and possible relevant effect of prednisolone treatment in AIN; however, based on the incidence of AIN we believe that a larger trial was not feasible. Thus, even if the trial does show a significant effect of prednisolone in AIN, such potential minor effect may still be discussed with patients based on the individual case.

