### Endpoints

#### Primary

eGFR 3 months after inclusion (eGFR for patients on dialysis at 3 months is defined as “0 ml/min/1.73 m^2^).

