### Statistics

The primary analysis will be performed as “intention to treat”, and the secondary analysis as “treated as”. Normally distributed variables are compared by unpaired t-test or one-way ANOVA. Repeated measures are analyzed using a general linear model (GLM). Comparable non-parametric tests are used in case of non-normally distributed variables. Both absolute and relative proportions are analyzed. Secondary end-points are analyzed as differences in absolute or relative proportions. Analysis of factors affecting the primary end-point will be performed using a GLM. Kaplan Meier curves will be used when appropriate e.g. in the evaluation of time to end stage renal failure. Any correlation between the primary end point and relevant secondary outcomes and outcomes form the exploratory analysis will be evaluated with appropriate adjustment for potential confounders.

Sample size was estimated for the primary outcome based on a clinical relevant 10 ml/min/1.73m^2^ difference in renal function (eGFR, CKD-EPI) between groups at 3 months, a standard deviation of 18 ml/min, a power of 0.80 and a significance level of 0.05. This showed that 51 patients should be included in each group. Anticipating dropouts, we estimate that 55 patients in each group are necessary and plan to randomize 110 patients.

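### The treated-as analysis offered as part of the answer to crossover gives up randomization; label it descriptive and add a complier-effect estimate beside intention to treat

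*Protocol article*

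**What the plan says.** In the protocol article, the Statistics section makes intention to treat the primary analysis "and the secondary analysis as" treated-as.

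The Discussion gives the reason: "An inevitable and direct consequence of the open-label design is a risk of cross-over between treatment groups", with preferences of patients or treating physicians as the example. It then presents the two analyses together as the way to deal with this, and continues that "a high cross over rate could influence and dilute a possible significant result, which is difficult to overcome statistically". It also concedes that dropout or crossover could leave the study underpowered. No expected crossover rate is given.

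The primary endpoint is "eGFR 3 months after inclusion (eGFR for patients on dialysis at 3 months is defined as" zero. On sample size: "Sample size was estimated for the primary outcome based on a clinical relevant 10 ml/min/1.73m^2^ difference in renal function", with "a standard deviation of 18 ml/min, a power of 0.80 and a significance level of 0.05". From these inputs the article arrives at 51 per group. The only stated inflation is for dropout: "Anticipating dropouts, we estimate that 55 patients in each group are necessary and plan to randomize 110 patients".

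The Background describes three large retrospective studies. In two of them the steroid-treated patients started with worse kidney function; in the third, baseline function was comparable. The Background and the Discussion both name selection bias as the weakness of such comparisons.

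**The concern.** A treated-as comparison is a comparison by choice. A control given prednisolone is moved into the treated group, and a patient in group B who does not take it is moved out. If controls who are not recovering are the ones given prednisolone, the treated group gains poor-prognosis patients and the untreated group loses them. The result is then biased against prednisolone by the mechanism that the article criticizes in the retrospective literature.

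The article does not say that the treated-as result is non-randomized. The confounder adjustment in the Statistics section concerns correlations between the primary endpoint and other outcomes, not this comparison.

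What is at stake is interpretation. If intention to treat gives an equivocal result, readers will turn to treated-as. If the two differ, they cannot tell dilution in one from selection in the other.

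**Working it through.** **1. The plan's own figure.** Per group, n = 2 × SD² × (1.960 + 0.842)² / difference² = 2 × 18² × 7.85 / 10² = 50.9, so 51. This reproduces the stated 51 (two-sided 0.05, normal approximation). The step to 55 implies 1 − 51/55 = 7.3% dropout and leaves no separate allowance for crossover.

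**2. Inputs for the check.** Difference 10 and SD 18 come from the Statistics section. The crossover fraction c and the correlation r between tendency to cross over and 3-month eGFR are assumptions. The base case is c = 20% of controls (none in the other direction) and r = 0.3 to 0.5.

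**3. Bias of treated-as.** Let the fraction c of controls with the worst latent prognosis cross over, and let φ be the normal density at that cut (φ = 0.280 for c = 0.20).

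- The treated group gains patients whose mean is low by r × 18 × φ / c. Its own mean falls by r × 18 × φ / (1 + c).
- The untreated group loses them. Its mean rises by r × 18 × φ / (1 − c).
- Bias = −r × 18 × φ × [1/(1 + c) + 1/(1 − c)]. For c = 0.20 the bracket is 0.833 + 1.250 = 2.083.
- r = 0.3: −0.3 × 18 × 0.280 × 2.083 = −3.15.
- r = 0.5: −0.5 × 18 × 0.280 × 2.083 = −5.25.
- r = 0: no bias.

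A simulation with 200,000 patients per arm agrees:

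| True effect | r | Treated-as | Intention to treat | Complier estimate |
|---|---|---|---|---|
| 0 | 0.3 / 0.5 | −3.24 / −5.25 | 0 | about 0 |
| 10 | 0.3 / 0.5 | 6.73 / 4.73 | about 8.0 | 9.9 / 10.0 |

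Intention to treat is diluted to 10 × (1 − 0.20) = 8.0, a shortfall of 2. At c = 0.20, treated-as is further from 10 once r exceeds 2 / (18 × 0.280 × 2.083) = 0.19.

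**4. At trial size, with crossover both ways.** 20,000 simulated trials per scenario, 51 per arm, and a different (logistic) crossover model. Rates are control to prednisolone / prednisolone to control; ranges run from moderate to strong dependence on prognosis.

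| Crossover | Treated-as mean, true effect 10 | Intention-to-treat mean, true effect 10 | Treated-as mean, true effect 0 | Treated-as false rejection |
|---|---|---|---|---|
| 10% / 5% | 7.3 to 5.7 | 8.5 | −2.7 to −4.4 | 11% to 23% |
| 20% / 10% | 5.2 to 2.7 | 7.0 | −4.8 to −7.4 | 27% to 55% |
| 30% / 10% | 4.2 to 1.2 | 6.0 | −5.8 to −8.8 | 36% to 69% |

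When crossover is unrelated to prognosis, treated-as averages 10.0 with about 5% false rejection. The complier estimate averages 10.0 to 10.2 throughout at a true effect of 10, with false rejection of 4% to 5% at a true effect of 0.

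**5. What the complier estimate does not do.** It is the intention-to-treat difference divided by (1 − total crossover), and its standard error is divided by about the same factor. At 51 per arm the intention-to-treat standard error is 18 × √(2/51) = 3.56. With 20% crossover of controls, the complier standard error is about 3.56 / 0.80 = 4.46. The ratios are 8.0/3.56 = 2.2 and 10/4.46 = 2.2, so the test is essentially the same. Power falls from 80% to about 61% either way. At 20%/10% crossover with strong dependence, simulated power was 52% for intention to treat and 49% for the complier estimate.

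**The case against.** The strongest reply is that intention to treat is primary, so the main inference keeps randomization. Treated-as as a secondary analysis is a familiar convention, and its detailed definition may stand in an analysis plan that is not shown. The first part stands: the bias touches only the secondary analysis and how it is read. The second part does not remove the point, because the article itself fixes treated-as and gives it the job of dealing with crossover. The mere absence of a complier estimate would not be a finding.

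A reader might infer three stronger things that the documents do not support.

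- **That the article is wrong to call dilution hard to overcome.** Its sentence is about a significant result, and the complier estimate does not restore power.
- **That treated-as is the only response to crossover, or that a better estimator comes free.** Intention to treat is named alongside it. The complier estimate has a wider interval and needs an exclusion restriction that is debatable here: the Discussion admits that open label may bias adjunctive therapy, dialysis is at the local investigator's discretion (Other treatment), and dialysis at 3 months scores as zero.
- **That severity-driven crossover is established.** The article cites preference and gives no rate, one of the three retrospective studies had comparable baselines, and the Other treatment section bars other immunosuppressive treatment during the study.

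It is also not shown that the exposure data needed are already collected. Table 1 and the Study treatment section describe medication recording and tablet counts for group B only.

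**Conclusion.** The point holds as a correction to the secondary analysis. Treated-as is not a sound way to deal with crossover, because its validity depends on crossover being unrelated to prognosis, and the article's own Background gives reason to doubt that. Under 20% control crossover and a correlation of 0.3 to 0.5 it is off by about -3 to -5 ml/min/1.73m², against a target difference of 10, and it can lie further from the effect of treatment than intention to treat does. Crossover rate and dependence on prognosis are assumptions; with no dependence the bias is zero. The primary analysis and the stated sample size are not affected by this point.

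**What to change.** 1. Keep intention to treat primary, unchanged.
2. Label treated-as descriptive and non-randomized, and do not present it as dealing with crossover.
3. Prespecify a supplementary complier average causal effect for 3-month eGFR: two-stage least squares with randomized arm as instrument, prednisolone received as exposure and day-0 eGFR as covariate. Define in advance what counts as having received prednisolone.
4. Record any prednisolone use in group A in the eCRF, and obtain 3-month eGFR as far as possible from everyone randomized, including those who cross over.
5. State the limits with the result: a wider interval, an effect for compliers only, monotonicity, an exclusion restriction open to doubt in this open-label design, and no recovery of power. The Discussion's sentence on dilution can stay.

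The cost is analysis wording plus one eCRF item if group A exposure is not already captured. No extra patients are needed.

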## Data Availability

Only the investigators will have access to the data. The datasets generated and analyzed during the current study are not publicly available but are available from the corresponding author on reasonable request. A dissemination plan has been developed which is directed towards different stakeholders a) Patients with chronic diseases, b) Health professionals, c) Politicians, d) Patient organisations, e) The general public, f) Scientific circles.

## Abbreviations

A1M: Alfa-1-mikrogolbulin
AIN: Acute interstitial nephritis
B2M: Beta-2-makroglobulin
BMP-7: Bone morphogenetic protein-7
eGFR: Estimated glomerular filtration rate
eCRF: Electronic Case report form
GLM: General linear model
IGFBP7: Insulin-like growth factor-binding protein 7
IL-18: Interleukin 18
KIM-1: Kidney injury marker 1
MCP-1: Monocyte chemotactic peptide-1
NAG: N-acetyl-beta-D-glucosaminidase
NGAL: Neutrophil gelatinase-associated lipocalin
PTH: Parathyroid hormone
TIMP-2: Tissue inhibitor of metalloproteinases-2
TGF-β1: Transforming growth factor-β1
